### Reference Standard Generation, Report Return, and Critical Findings

The radiologists are responsible for producing the ground-truth (reference standard) for all CXR images during the study. The first step in ground-truth generation is to assign 2 thoracic radiologists to independently interpret the CXR images to set up the reference standard, classifying each finding as “normal” or “abnormal.” The correct classification matches the reference standard. For cases classified as *abnormal*, the presence or absence of the relevant radiological findings (consolidation, pulmonary opacity, pneumothorax, atelectasis, pleural effusion, and cardiomegaly) will be assessed, as well as the presence or absence of changes suggestive of TB. Based on these evaluations by the 2 thoracic radiologists, the ground truth is established. The radiologists will be blinded to both the physicians’ interpretations and the AI outputs.

A chest radiograph will be labeled as suggestive of pulmonary TB if at least 1 radiographic feature considered compatible with pulmonary TB is present, as determined by the adjudicated thoracic radiologist reference standard. Examples include cavitation, upper-lobe–predominant consolidation or opacities, fibronodular changes or scarring with upper lobe volume loss, or a miliary pattern. If none of these features is present, the examination will be labeled as “not suggestive of pulmonary TB.”

For physician performance analyses, an examination will be considered correctly classified when the physician’s binary classification (normal vs abnormal; suggestive vs not suggestive of pulmonary TB; presence or absence of specific radiographic patterns) matches the adjudicated thoracic radiologist reference standard. In cases of any disagreement between the 2 experts in any of the evaluated items, a third radiologist, more senior, will adjudicate.

All findings will be registered in the CARPL, with abnormalities annotated to allow direct comparison with AI outputs. This will serve as the reference value for model validation and performance analysis (Figure 4).

**Figure 4. F4:**
[figure not shown]
Workflow for reference standard generation, report return, and critical findings alerts. (A) Each chest X-ray (CXR) is assigned an encrypted patient ID before being uploaded for analysis. (B) Blinded thoracic radiologists independently interpret the images to establish the reference standard. Final reports are uploaded to the cloud and returned to the clinical site via the app or registered email, with decrypted patient identifiers accessible only to the site. (C) If a radiologist identifies a potentially critical finding, such as tension pneumothorax, a large pulmonary mass, or near-complete lung consolidation, an automated alert is immediately sent to the cluster via email or app notification. All personal data remain encrypted throughout the process. AI: artificial intelligence.

Patient identifiers will be used solely to return reports of critical imaging findings to clinical sites, when present. These identifiers are cryptographically isolated from the research dataset and are never accessible to the research team (Figure 4). If the radiologist identifies a potentially critical finding, such as tension pneumothorax, a large obstructive mass, or near-complete lung consolidation, an alert will be sent to the originating site via email and/or phone (Figure 4). Patient data will remain encrypted; only the automated system will link the alert to the corresponding patients, ensuring privacy and prompt clinical follow-up. An institutional lifetime license ensures consistent labeling with the same software version throughout the study.

At the end of the study, all participating physicians and radiologists will be invited to complete a standardized questionnaire assessing the usability of the LuAna platform and its integration into routine clinical workflows. Responses will be used to address implementation challenges and opportunities for improvement (Multimedia Appendix 1).

### Data and Safety Monitoring Board

An independent Data and Safety Monitoring Board, comprising external experts in clinical trials, radiology, statistics, and ethics with no conflicts of interest, will oversee the study in accordance with international guidelines and good clinical practice. The board will be responsible for safeguarding patient safety and ensuring study integrity.

### Statistical Analysis

The sample size was calculated to detect a minimum difference of 10% in the primary outcome—a binary indicator of whether the physician correctly labeled a CXR—between the AI-assisted and control groups. The calculation accounted for the stepped-wedge cluster-randomized design with batched implementation using the following assumptions: 9 clusters randomized in 3 batches to cross over from control to intervention, 10 time periods, a baseline detection rate of 67% in the control group, an expected increase to 77% in the intervention group, and an intracluster correlation coefficient ranging from 0.001 to 0.003.

The design effect was adjusted for the correlation structure induced by repeated measures within clusters over time using methods described by Hussey and Hughes [28] and extended to account for batched randomization, as described by Hemming et al [35,36]. The power calculation targeted 80% power at a 2-sided significance level of 5% and accounted for potential variability in cluster sizes. The final average cluster size was 37, and the overall sample size was inflated by 10% to account for anticipated exclusions due to image quality issues or missing data (dropout). This approach ensures adequate power to detect a meaningful effect of the intervention while maintaining the integrity of the stepped-wedge design with staggered implementation across batches.

Primary analysis will follow the modified intention-to-treat principle. All eligible CXRs (the unit of analysis in this study) will be analyzed according to the study group (control or intervention), to which their corresponding cluster was allocated at the time of image acquisition, regardless of physician adherence to the intervention or exposure to AI output. Images of poor quality, as defined by our radiologists, will be excluded postrandomization.

The primary outcome analysis will use a generalized linear mixed model with a binomial distribution and logit link function to estimate the effect of the AI-assisted intervention on detection probability. The model will include fixed effects for the intervention group (AI-assisted vs control), calendar time (to adjust for secular trends), time since intervention rollout (to account for learning or adaptation effects), and batch effects. In addition, random intercepts for clusters will be specified to account for intracluster correlation.

Results will be reported as adjusted odds ratios with 95% CIs and 2-sided *P* values. Model fit and assumptions will be evaluated using the Residual Diagnostics for Hierarchical (Multilevel/Mixed) Regression Models (DHARMa) [37]. In case of convergence issues or model instability, generalized estimating equations with robust SEs will be used as an alternative to estimate population-averaged effects. Independent models will also be fitted for each radiological finding, as well as for the pulmonary abnormality and TB algorithm.

Model performance metrics will be reported with 95% CIs [38,39]. Responses to questions regarding the mobile interface will be summarized as frequencies. Chi-square test and ordinal logistical regression will be used to investigate associations between these responses and physician characteristics (eg, years in practice and biological sex). Additionally, generalized linear mixed models will be fitted with the algorithm’s output as the dependent variable, adjusted for image characteristics, to investigate their effect on AI classification.

Missing data are expected to be minimal due to app-enforced completeness checks. Incomplete records will be described, and sensitivity analyses using multiple imputation will be performed if the proportion of missing data exceeds 10%. All analyses will be performed in R (R Foundation for Statistical Computing), and code scripts will be version-controlled and archived to ensure reproducibility.

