**Methods:**

This study is a protocol for a multicenter, stepped-wedge, cluster-randomized clinical trial following the CONSORT-AI (Consolidated Standards of Reporting Trials-Artificial Intelligence) extension and SPIRIT-AI (Standard Protocol Items: Recommendations for Interventional Trials-Artificial Intelligence) guidelines. The intervention involves the diagnostic support solution for chest radiography, Lung Analysis (LuAna), an AI-powered chest X-ray interpretation tool developed in partnership with the Brazilian Ministry of Health. Across 9 cities in Brazil, clusters will transition monthly from unaided chest X-ray interpretation by general practitioners to AI-assisted interpretation, with performance benchmarked against thoracic radiologists. The stepped-wedge design ensures that all clusters receive the intervention, reflecting real-world coordination, enhancing acceptability, improving statistical power, and strengthening causal inference through repeated measures. Diagnostic performance will be compared with a reference standard established by thoracic radiologists.

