**Results:**

This project was funded in October 2024 (following ethics approval by the institutional review board). Data collection commenced in January 2026 and is projected to be completed by September 2026, marking the end of the trial period. As of November 2025, 3 centers were fully prepared for enrollment initiation. The LuAna clinical trial is currently ongoing, with data analysis (including statistical analyses) forecasted to be finalized by November 2026. Results are expected to be published by January 2027.

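### The printed average cluster size of 37 cannot give 80% power if it is per city, its unit and total are not stated, and ten monthly periods do not fit January to September 2026

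*Protocol article*

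**What the plan says.** All the planning figures are in the Statistical Analysis section of the protocol article. The design is "9 clusters randomized in 3 batches to cross over from control to intervention, 10 time periods", with "a baseline detection rate of 67% in the control group" and "an expected increase to 77% in the intervention group". The intracluster correlation is 0.001 to 0.003. "The power calculation targeted 80% power at a 2-sided significance level of 5" per cent, using the Hussey and Hughes method extended to batches, with an unquantified allowance for unequal cluster sizes. The result is given as: "The final average cluster size was 37, and the overall sample size was inflated by 10" per cent. No total is printed.

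The Study Design section makes cities the clusters, has them cross over at monthly intervals, and says every cluster eventually receives the intervention. The abstract agrees: "clusters will transition monthly from unaided chest X-ray interpretation". On timing, the abstract says: "Data collection commenced in January 2026 and is projected to be completed by September 2026". The Results section repeats those dates.

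**The concern.** Two sets of figures do not agree as printed.

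- **Size and power.** With cities as clusters, a cluster size of 37 is 37 films per city for the whole trial. That total is small for a ten-point difference in proportions, before any loss from clustering or adjustment for time.
- **Calendar.** The calculation uses "10 time periods" and the steps are monthly, but the stated window contains nine months.

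The Statistical Analysis section concludes that power is adequate, and data collection is under way. A reader cannot tell whether the trial needs a few hundred films or a few thousand, or whether the layout that was powered is the one that fits the calendar.

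**Working it through.** **Inputs from the article:** 9 cities, 3 batches, 10 monthly periods, 67% versus 77%, ICC 0.001 and 0.003, two-sided 5%, 80% power, cluster size 37, 10% inflation. **Assumed here:** batch length and stagger (Figure 2 is not shown), three cities per batch crossing in consecutive months, and equal cluster sizes unless stated.

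**1. Individually randomised benchmark.** Per arm:

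(1.96 + 0.8416)² × (0.67×0.33 + 0.77×0.23) / 0.10² = 7.849 × 0.3982 / 0.01 ≈ 312.5

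This is 313 per arm or 626 films in all (632 with the pooled-variance formula).

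**2. Reading A: 37 per city in total.** N = 9 × 37 = 333. The inflated total is 333 × 1.1 ≈ 366, or 333 / 0.9 = 370. The average variance is v = 0.3982 / 2 = 0.1991. Ignoring clustering and time:

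SE = √(4 × 0.1991 / 333) = 0.0489; power = Φ(0.10/0.0489 − 1.96) ≈ 53%

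Even if all 370 films were analysable, power would be about 57%. With a random city intercept and fixed period and batch effects (generalised least squares variance), 333 films give about 14–38%, depending on layout. No layout examined approaches 80%.

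**3. Reading B: 37 per city per month.** Same variance formula, power = Φ(0.10/SE − 1.96), with period effects shared across batches:

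| Layout over 10 months | City-months | Films | Power at ICC 0.001 / 0.003 |
|---|---|---|---|
| 4-period batches, 3 months apart | 36 | 1332 | 75.8% / 72.8% |
| 6-period batches, 2 months apart, crossing after months 1–3 | 54 | 1998 | 83.4% / 81.6% |
| Same, crossing after months 2–4 | 54 | 1998 | 78.8% / 76.7% |
| 8-period batches, 1 month apart | 72 | 2664 | 84.6% / 83.3% |
| Batches followed to month 10 | 63–81 | 2331–2997 | 84.7–93.2% over both ICCs |
| No batching, one city per month | 90 | 3330 | 99.7% / 99.2% |

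Variations on these:

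- With batch-specific period effects, the batched layouts all fall to about 73–76%.
- The 4-period layout needs about 41.5–45 films per city-month for 80%.
- If 37 is already inflated (33.3 analysable), the 8-period layout gives 80.8% / 79.4%.
- With a cluster-size coefficient of variation of 0.4, the 6-period layout (first crossing rule) gives 82.1% / 80.4%.

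The plan's 80% therefore lies inside the range for Reading B, but cannot be reproduced without the layout. The implied total runs from 333 to 3330 across the two readings.

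**4. Calendar.** January to September inclusive is 9 months and ten monthly periods need 10. Dropping period 10 at 37 per city-month gives:

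| Layout | Power at ICC 0.001 / 0.003 | AI-assisted months for the last city |
|---|---|---|
| 4-period, 3 months apart | 75.8% / 72.7% | 0 |
| 6-period, 2 months apart (crossing after months 1–3) | 83.4% / 81.6% | 2 |
| 8-period, 1 month apart | 84.6% / 83.2% | 4 |
| Followed to the end, 3 months apart | 89.7% / 88.5% | 0 |
| No batching | 99.7% / 99.1% | 0 |

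The largest loss, about 4 points, is in the layout with batches 3 months apart followed to the end (from 93.2% / 92.5%).

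**The case against.** The strongest reply is that Reading A is not what was meant. In a Hussey and Hughes calculation the size entered is commonly per cluster-period, and 37 films per city over ten months is under four a month in cities that contain several health care units. On Reading B, batched layouts consistent with the text reach 80%. The layout is in a figure not available here, and a journal article may leave the total and the batch schedule to the full protocol. Nothing in the article makes 37 a recruitment cap. The September date is only a projection.

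Much of this stands. A reader might infer that the figures cannot be reconciled on any reading, so that the stated power and size are wrong. The documents do not support that: 6- and 8-period batches give about 82–85%, and no total is printed that could be wrong. A reader might also infer that one city will certainly go unexposed; that follows only in some layouts.

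The reply does not remove the point. The article prints 37 as a cluster size after defining clusters as cities, and the figure taken that way cannot support the printed power. Nor does it explain how ten monthly periods fit nine months.

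**Conclusion.** The point holds in a limited form. As printed, 37 per city gives 333 films and at most about 53% power, or about 14–38% in a stepped wedge, against a target of 80%. This needs only the printed figures for the upper bound. If 37 is per city per month, power is about 73–93% across the staggered batched layouts examined. Whether the target is met then depends on batch length, stagger, crossing months and whether period effects are shared between batches; these layouts are assumptions of this check.

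The ten-period and nine-month statements contradict each other whatever the layout. The power cost is 0–4 points. The more important consequence depends on layout: with one city crossing per month, or with batches 3 months apart (4-period, or followed to the end), the last city would have no AI-assisted month, contrary to the statement that all clusters receive the intervention.

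**What to change.** In the Statistical Analysis section:

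- State what 37 counts (per city, or per city per month) and whether it is before or after the 10% inflation.
- Give the total number of films before and after inflation.
- Set out the periods and crossing months for each batch, and restate power for that layout at ICC 0.001 and 0.003, using the period and batch effects of the planned model.
- Either move the end of data collection so that it covers ten monthly periods, or restate the design and power for nine and confirm that every city has at least one AI-assisted month.

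The cost is a recalculation and some rewording. The restated power may be slightly less favourable, or the end date may move by one month.

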#### Exclusion Criteria

CXRs performed for peripherally inserted central catheter line positioning, preoperative risk assessment, lung cancer screening, or trauma-related evaluation will be excluded. In addition, radiographs printed on plain paper and examinations with technical quality below the minimum acceptable standard will also be excluded.

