**Figure 3. F3:**
[figure not shown]
Workflow for chest X-ray (CXR) interpretation in control and intervention groups. Top panel (control group—without AI): CXRs from patients with respiratory complaints are interpreted solely by the physician (1), without access to AI support (2). Bottom panel (intervention group—with AI): physicians first perform an initial assessment of the CXR (1) and register their findings via the LuAna mobile app (2). After this, the AI model processes the image and returns a score and a heatmap highlighting abnormal regions (3). The physician can then review and, if needed, revise their interpretation based on the AI output (4). Both pre- and post-AI interpretations are recorded for analysis. For both groups, CXR assessments are compared against a reference standard, defined as thoracic radiologist evaluation performed on the CARPL, with reports independently double-validated by thoracic radiologists blinded to both the physician assessment and AI output. The primary outcome is the comparison of radiologic findings detection rates before and after AI assistance relative to the reference standard. The workflow includes data acquisition at the study centers, followed by radiologist annotation, primary and secondary end point evaluation, and statistical analysis at the coordinating center. AI: artificial intelligence; CARPL: Clinical Artificial Intelligence Research Platform for Labeling.

Only demographic variables, including age group, sex, and race, will be collected in aggregated form to characterize the study population and allow for fairness analyses, ensuring equitable and unbiased AI performance. CXRs will be captured either by photographing printed films positioned on a lit negatoscope, by photographing digital images displayed on a picture archiving and communication system monitor, or by direct screen capture, all following strict protocols to guarantee full anonymization. Physicians will capture only the thoracic image, ensuring that all patient identifiers are systematically removed and never visible. A patient ID entered solely to return the radiologist’s report to the local health unit will be encrypted and remain inaccessible to the research team. Nondiagnostic images or studies failing predefined quality-control criteria will be excluded from analysis.

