## Discussion

### Principal Findings

This trial is a pivotal effort to evaluate how AI can enhance diagnostic accuracy, clinical workflows, and physician performance in interpreting chest radiographs.

By using a batched stepped-wedge cluster-randomized design across a nationally representative sample of health care settings, we aim to rigorously assess the real-world utility of LuAna, an AI-powered platform for CXR interpretation developed in the public sector to assist general practitioners.

Despite ongoing debate about the advantages of SW-CRTs, including concerns about equipoise and delayed access to interventions [41], this design offers distinct benefits for implementation research. Governed by the same ethical principles as all clinical research [42], SW-CRTs are particularly valuable when evaluating innovations that are expected to be beneficial and for which withholding access may be contentious [42]. In the SUS context, this approach ensures that all centers ultimately gain access to AI support, promotes fairness and acceptability, and provides a pragmatic pathway to sustainable integration of the intervention into routine care.

The central goal is to determine whether LuAna improves clinicians’ ability to detect radiographic abnormalities, particularly in environments with limited access to radiology expertise. Comparisons against adjudicated, double-blinded radiologist interpretations will enable the quantification of diagnostic agreement, while stratified analyses by site type and physician characteristics will offer insights into contextual factors that may influence AI performance.

Importantly, the trial also investigates the clinical impact beyond diagnostic accuracy. By evaluating patient management decisions and turnaround times, we aim to capture how AI affects treatment pathways and efficiency in routine care. Usability assessments will provide critical feedback for refining and scaling the platform, thereby ensuring seamless integration into diverse clinical workflows across both mobile and desktop interfaces.

Robustness will be evaluated through sensitivity analyses on image quality, artifacts, and medical devices, thereby validating the model’s generalizability under real-world conditions. Additionally, longitudinal analysis of physician interpretations will explore whether repeated AI exposure improves independent performance, highlighting AI’s potential educational role.

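### The image-quality exclusions are not confined to the primary analysis: they cut off the low end of the planned photo-quality and robustness analyses and, if they differ by phase, could modestly shift the primary contrast

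*Protocol article*

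**What the plan says.** Three places in the protocol article remove images on quality grounds, each in different terms.

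- Exclusion Criteria, as an eligibility rule: "examinations with technical quality below the minimum acceptable standard will also be excluded".
- Data Collection (text after Figure 3), as a general rule: "Nondiagnostic images or studies failing predefined quality-control criteria will be excluded from analysis".
- Statistical Analysis, at the end of the paragraph on the primary analysis: "Images of poor quality, as defined by our radiologists, will be excluded postrandomization". That paragraph opens with "Primary analysis will follow the modified intention-to-treat principle".

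Three other places need variation in image quality.

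- Statistical Analysis plans mixed models with the algorithm's output as the dependent variable, adjusted for image characteristics.
- Textbox 1 makes the association of AI output with photo quality, thoracic devices and technical artifacts a secondary outcome. It also lists AI performance in a real-world setting as a secondary objective.
- Principal Findings says: "Robustness will be evaluated through sensitivity analyses on image quality, artifacts, and medical devices".

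On who makes the image and who judges it, Data Collection says "Physicians will capture only the thoracic image, ensuring that all patient identifiers are systematically removed and never visible", and the reference-standard section says "The radiologists will be blinded to both the physicians’ interpretations and the AI outputs". Blinding to phase or to acquisition date is not mentioned. The sample size carries a 10% inflation for image-quality exclusions and missing data together, with no split by phase.

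**The concern.** Two things are at stake.

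**Secondary and robustness analyses.** Photo quality is an explanatory variable in one planned model and the subject of promised sensitivity analyses. A rule that takes failing images out of analysis, with no exception, truncates that variable at its low end. That is where a photograph-based tool is most likely to be tested, and the Limitations section itself names variation in capture as something that may affect the algorithm. Sensitivity and specificity in routine use would then describe acceptable captures only.

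**Primary contrast.** Every image is acquired after the clusters have been allocated, by physicians who know whether AI is switched on. In control the capture serves the reference reading. In intervention the same capture also feeds the AI. Care in taking it, and so the share later excluded, could differ by phase. Blinding the radiologists to reads and AI output stops exclusion from following the outcome directly, but does not remove a difference that arises at capture.

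**Working it through.** **1. The rules set beside the analyses they touch**

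| Analysis | Needs a reference label? | Are excluded images kept? |
|---|---|---|
| Physician accuracy (primary) | Yes | No (Statistical Analysis, Data Collection) |
| AI sensitivity, specificity, AUC | Yes | No (Data Collection, general wording) |
| AI output on image characteristics | No for the outcome, which is the AI output; quality is labelled by the radiologists | Not stated; Data Collection as written says no |
| Robustness to image quality | Depends on the form used | Not stated |

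The third row loses films without need: a film too poor for a reference label still has an AI output and can be labelled as poor.

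**2. Possible shift in the primary contrast**

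The protocol gives no exclusion rate by phase, so there is no plan figure to reproduce. Inputs:

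- P = 67%, accuracy over all films: the control rate in Statistical Analysis, used in both phases so that there is no true effect.
- e = share excluded in a phase (assumed).
- q = accuracy in the excluded films (assumed).

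Retained accuracy = (P − e·q) / (1 − e). Shift = retained accuracy in intervention minus retained accuracy in control.

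Worked case, q = 50%:
- e = 5%: (0.67 − 0.025) / 0.95 = 67.9%
- e = 10%: (0.67 − 0.050) / 0.90 = 68.9%
- e = 15%: (0.67 − 0.075) / 0.85 = 70.0%

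So 5% against 10% shifts the contrast by 1.0 point, and 5% against 15% by 2.1 points.

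| Excluded, control | Excluded, intervention | q = 60% | q = 50% | q = 40% |
|---|---|---|---|---|
| 10% | 10% | 0.0 | 0.0 | 0.0 |
| 5% | 10% | +0.4 | +1.0 | +1.6 |
| 5% | 15% | +0.9 | +2.1 | +3.3 |

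A smaller gap, 8% against 12% with q = 45%: (0.67 − 0.036) / 0.92 = 68.9% and (0.67 − 0.054) / 0.88 = 70.0%, a shift of +1.1 points.

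All signs reverse if more control films are excluded. If q = P, the formula returns P whatever e is, so the shift is zero.

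**3. What is estimated even when exclusion is balanced**

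Suppose 10% are excluded in both phases and AI adds nothing on those films. A true effect of 10.0 points over all films becomes 10.0 / 0.90 = 11.1 points in the retained films. This is a narrower target population rather than a phase imbalance.

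**The case against.** The rule is disclosed and judged without sight of the outcome. Technical quality is an eligibility criterion, the analysis is labelled modified intention-to-treat, exclusions are budgeted for, and the criteria are called predefined in Data Collection. Because each cluster's sequence is fixed before its films are taken, quality screening by radiologists can only come after randomisation. Tables of exclusions and the detail of the criteria may sit in a document not shown. All of this stands. It removes any suggestion of exclusion driven by results, but it does not limit the general wording in Data Collection.

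The size of the shift is also open to challenge. What might vary by phase is care over the photograph. The physician reads the film or monitor directly, so a careless photograph does not make that reading harder. In control it can affect measured accuracy only through a noisier reference label; in intervention it can also act through the AI output. Low accuracy belongs to technically hard films, and nothing suggests that their share differs by phase. This pushes q towards P and the shift towards the lower end of the range. The suggested mechanism (more care when the capture feeds the AI) would exclude fewer intervention films and so work against the AI. A 5% against 15% split also spends the whole 10% allowance on image quality alone, if the phases are of similar size. These points stand.

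A reader might go further and infer that the rule takes away all the films the photo-quality analysis needs and guarantees a finding of robustness. The documents do not support that. Retained films still differ in quality, devices and artifacts, so the models can be fitted; what is lost is range. The Statistical Analysis sentence belongs to the primary-analysis paragraph, so this part rests mainly on Data Collection. Nor would a worst-case bound, with every excluded film right in one phase and wrong in the other, be informative: it would apply to any trial with the same loss.

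**Conclusion.** The point holds in a limited form. As written, quality exclusions apply to analysis in general. They restrict the photo-quality and robustness analyses to the upper part of the quality range and confine AI performance to acceptable captures. This follows from the text and needs no assumption.

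The effect on the primary contrast is a possibility, not an established bias. It needs exclusion, or the accuracy of the excluded films, to differ by phase. Under assumed differences of 4 to 10 percentage points in exclusion and 40% to 60% accuracy in excluded films, the shift is roughly 0.4 to 3 points, in either direction, against a 10-point target. With no true effect it is zero if both quantities are equal across phases. A reader might conclude that the primary result is compromised; the documents do not show that. They leave open a modest shift that reporting by phase and one sensitivity analysis would reveal.

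**What to change.** - State one quality criterion in place of three wordings, and have it applied by radiologists who are blinded to phase as well as to reads and AI output.
- Limit exclusion from the physician-accuracy analysis to films those radiologists cannot label. Alternatively, keep the present rule and add a sensitivity analysis of the primary outcome that includes all gradable poor-quality films.
- Report the number and share of excluded films by phase.
- Keep every film with an AI output in the model of AI output on image characteristics, whatever its quality.
- Report AI performance with and without gradable poor-quality films.

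The cost is a change of wording and one or two extra analyses of images already captured. The drawback is a noisier reference label for films at the margin of quality, which is why both sets of AI results should be shown. The rule should be fixed before any comparison by phase is seen.
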